# Single dose of intravenous ferric carboxymaltose infusion versus multiple fractionated doses of intravenous iron sucrose in the treatment of postoperative anaemia in colorectal cancer patients: study protocol for a randomised controlled trial

**DOI:** 10.1186/s13063-018-3125-2

**Published:** 2019-01-07

**Keywords:** Colorectal cancer, Postoperative anaemia, Intravenous iron

## Abstract

**Background:**

Patients with colorectal cancer (CRC) often present with associated anaemia which is usually present at the time of diagnosis and is aggravated during the postoperative period due to blood loss during the surgery process. Several guidelines advocate for the treatment of postoperative anaemia in these patients in order to prevent complications and allogeneic blood transfusions. However, there are no publications to shed light on the effectiveness of intravenous iron (IVI) administration after CRC surgery and the optimal dose and regimen. We have started a clinical trial with the objective of comparing the effectiveness of 1000 mg of ferric carboxymaltose with fractionated iron sucrose 200 g/48 h for the treatment of postoperative anaemia, by measuring the change of haemoglobin (Hb) levels from postoperative day (POD) 1 to POD 30.

**Methods:**

We designed an open label randomised controlled trial to compare two postoperative IVI treatment regimens. Patients aged > 18 years undergoing CRC surgery, with Hb < 11 g/dL on POD 1 are randomly assigned to receive either 1000 mg of ferric carboxymaltose (single dose) or 200 g/48 h of iron sucrose. The main study endpoint will be the change from POD 1 to POD 30 in Hb levels and the key secondary endpoint the percentage of patients with Hb levels ≥ 13 g/dL at POD 30. Other secondary endpoints include: changes in iron metabolism parameters (Fe, ferritin, transferrin, % saturated trasferrin) at POD 30; total doses of iron received; number of postoperative transfusions; compliance with oral iron treatment; number of medical and surgical complications; adverse reactions reported by the patient; use of health resources after surgery; and changes in quality of life (QoL). It has been estimated that a sample of 48 patients per group will allow detecting a difference of 0.75 g/dL in Hb in the change in Hb levels from POD 1 to POD 30.

**Discussion:**

The results of this study will confirm if the single dose of 1000 mg ferric carboxymaltose should be preferred in front of the fractionated doses and in which type of patients this regimen should be used preferably.

**Trial registration:**

European Union Clinical Trials Register, EudraCT 2015-001005-13. Registered on 6 January 2015.

**Electronic supplementary material:**

The online version of this article (10.1186/s13063-018-3125-2) contains supplementary material, which is available to authorized users.

## Background

Patients with colorectal cancer (CRC) often present with associated anaemia which can be attributed mainly to iron deficiency due to blood loss and to the inflammation inherent to neoplastic processes [1]. Anaemia is usually present at the time of diagnosis and is aggravated during the postoperative period due to blood loss during the surgery process. On the other hand, it has been well established that preoperative anaemia increases the risk of allogeneic blood transfusions during the perioperative period and that transfusions are associated with an increase in postoperative infections, a higher rate of tumour recurrences and an increase in five-year mortality [1–3]. This is why alternative strategies to optimise patients with preoperative anaemia have been implemented to avoid transfusions. Intravenous iron (IVI) has been shown as an efficacious alternative to transfusion [4–7] and is now recognised as more effective than the oral route in this setting. The main reasons why oral iron has been superseded by IVI are malabsorption due to the inflammation associated to the neoplastic process and the poor compliance due to gastric intolerance [8–10].

The optimisation of CRC cancer patients with anaemia before undergoing surgery was well established in our centre a decade ago, after a multidisciplinary team implemented a diagnostic track for this type of patients [11]. According to the diagnostic track, all patients presenting with anaemia at the time of diagnosis should be treated before surgery with IVI. An expert consensus of different Spanish scientific societies addresses the management of anaemia in surgical procedures with medium-high bleeding, such as CRC surgery, and advises that it would be desirable to reach haemoglobin (Hb) levels > 13 g/dL before surgery in order to minimise the risk of transfusion and quickly correct the anaemia [10, 12]. However, although this document also recommends treatment of postoperative anaemia with IVI with the aim of minimising transfusions and complications, there is no robust evidence to endorse this recommendation.

Titos et al. describe a retrospective study [13] where treatment with IVI after CRC surgery did not affect the needs of transfusion nor did it significantly increase Hb levels. However, it has to be taken into account that the sample size was small and that patients were only studied up to the moment they were discharged; thus, doses received could have been insufficient to induce a significant increase in Hb levels.

Currently, the trend in CRC surgery is to initiate food intake and mobilisation as soon as possible to achieve a prompt functional recovery of the patient and eventually shorten hospital stay. In this situation, the treatment of postoperative anaemia in patients with CRC should be done early and preferably by IV route, as the patient is discharged very soon after surgery.

In our hospital, there is an established protocol for the treatment of postoperative anaemia when it is detected in these patients, aiming at the normalization of Hb levels. This protocol establishes that all patients intervened for CRC, independent of the Hb levels and iron status, must receive during the early postoperative period 200 mg of IVI to substitute the intraoperative loss of blood. On postoperative day (POD) 1, patients must have blood tests with a haemogram. If Hb is < 11 g/dL patients will receive one dose of 1000 mg of ferric carboxymaltose. If Hb is between 11 and 13 g/dL, patients receive 200 mg/48 h of iron sucrose during hospital stay until iron deficit is solved (calculated according to Ganzoni Formula) and after hospital discharge, they will be prescribed oral iron in case the target doses have not been completed. To implement this protocol, two formulations are available at our institution: ferric carboxymaltose 500 mg strength and iron sucrose 100 mg strength.

Despite the advantages of the single 1000-mg doses of ferric carboxymaltose administration, that would guarantee that patients receive the iron load needed before hospital discharge. In a recent retrospective study, we observed an underuse of the 1000-mg single dose even in patients with low Hb levels [14]. On the one hand, the difference in cost compared to fractionated formulations of iron sucrose may account for this. However, the lack of acceptance of such protocols may also be related to the limited evidence perceived by surgeons of the benefit of the 1000-mg doses over the fractionated doses. In fact, there is a lack of information of which is the clinical impact of the two different approaches. Thus, we have considered that comparing both schemes would give an answer to a relevant clinical question that may impact clinical practice in the future. Our hypothesis is that treatments with a single dose of ferric carboxymaltose in patients who present with Hb levels < 11 g/dL at POD 1 will be more effective in achieving normal Hb levels at POD 30.

## Participants and methods

### Study design and interventions

This is a single-centre, open-label randomised controlled trial to compare the effectiveness of two different IVI regimens to treat postoperative anaemia in patients undergoing CRC surgery. During the visit before surgery with the anaesthesiologist, patients meeting the eligibility criteria will be informed and those willing to participate will sign the informed consent form. On POD 1, Hb levels will be determined and those patients presenting with levels < 11 g/dL will be randomly assigned to one of the following study treatments: (1) single dose of 1000 mg of ferric carboxymaltose (Ferinject®, Vifor, France) intravenously in a 15-min infusion; or (2) repeated doses of 200 mg of iron sucrose (different brand names) every 48 h from POD1 up to hospital discharge or up to the total dose equivalent to iron deficit calculated according to the Ganzoni formula, whichever occurs first. Patients who are discharged before achieving the calculated doses will be prescribed oral iron up to POD 30. Patients with Hb levels ≥ 11 g/dL on POD 1 will not be included in the study and will follow the treatment according to hospital protocols. After discharge, patients will be followed up to POD 30 (Fig. 1).

**Fig. 1 Fig1:**
[figure not shown]
Study design. Ganzoni Formula: Total iron dose (mg iron) = body weight (kg) × (target – actual Hb) (g/dL) × 2.4 + iron for iron stores (mg iron)*. *Iron stores: body weight < 35 kg = 15 mg/kg body weight; body weight > 35 kg = 500 mg

### Study population

Patients aged > 18 years undergoing programmed CRC surgery, with Hb levels < 11 g/dL on POD 1 and who have signed the informed consent form (ICF) are included in the study. Patients who present with Hb levels ≥ 11 g/dL on POD 1, with anaesthetic risk ASA 4, with Claviens classification of surgical complications grade 4, pregnant or lactating women, and patients with previous known intolerance/adverse reactions or with contraindications to IVI are excluded.

### Randomisation

A computer-generated block randomisation (block size 8) has been created with WinPepi etcetera module version 3.26. Randomisation has been stratified by Hb level on day 1 (Hb < 10 g/dL or Hb ≥ 10 g/dL). Sealed envelopes have been created for each individual patient. Pre-screened patients are randomly assigned to one of the two study treatments on POD 1 and after knowing the results of the blood tests for Hb levels.

### Study procedures

During the preoperative anaesthesiology visit, patients meeting eligibility criteria will be informed and those willing to participate in the study will sign the ICF. During this visit, and after signing the ICF, patients will complete a quality-of-life questionnaire (QL-C30). On POD 1, and after checking eligibility (Hb levels < 11 g/dL), treatment will be randomly assigned to one of the two treatment arms. After hospital discharge, patients will come for a visit on POD 30 when blood tests assessing iron metabolism and Hb will be performed and patients will be asked to complete the QL-C30 questionnaire. Any additional blood tests assessing Hb levels and iron metabolism performed from patient diagnosis to end of trial (i.e. at diagnosis, immediately before surgery and on POD 4 or hospital discharge) will be recorded. When patients are hospitalised, regular checks for adverse events or any complication are performed. Iron treatment will be discontinued in patients admitted in the intensive care unit on POD 1 due to organic fail or presenting Claviens grade 4 complications. Whenever possible, these patients will be followed up to POD 30 (Fig. 2).

**Fig. 2 Fig2:**
[figure not shown]
Schedule of enrolment, interventions and assessments

### Study endpoints

The main study endpoint will be the change in Hb levels from POD 1 to POD 30. The percentage of patients with Hb levels ≥ 13 g/dL at POD 30 will be considered as a key secondary endpoint. Other secondary endpoints include: changes in iron metabolism parameters (Fe, ferritin, transferrin, % saturated trasferrin) at POD 30; total doses of iron received up to POD 30; number of postoperative transfusions; percentage of patients not compliant with oral iron treatment; number of medical and surgical complications; adverse reactions reported by the patient; and use of health resources after surgery: number of admissions, length of hospital stay; changes in quality of life (QoL). Potential adverse reactions of IVI are headache, dizziness, nausea, abdominal pain, constipation, diarrhoea, exanthema, hypophosphatemia and increases in alanine-aminotransferase. Hypersensitivity and injection site reactions are rare. Oral iron treatment is associated with gastric intolerance and constipation.

### Data collection and management

Study data will be collected in paper case report forms (CRF) designed for the study. Risk adjusted monitoring will be performed by personnel independent from the investigator team, consisting on checking all informed consent forms and completeness of all CRFs and source data verification for a random sample of patients. Data will be entered in the study database by members of the study team. Patients will be identified by a numerical code and no personal information will be included in the paper CRF and the database.

### Statistical methods

#### Sample size

Our hypothesis is that the difference in change in Hb levels (primary endpoint) between the two studied regimens will be 0.75 g/dL. With a two-sided risk of 5% and a power of 80%, and assuming a common standard deviation of 1.3, a total of 48 evaluable patients per group are to be included.

#### Populations of analysis

For safety analysis, all patients who have received at least one dose of IVI will be considered, in the group of treatment they actually received.

The intention to treat (ITT) population will consist of all randomised patients with at least one Hb measurement after POD 1. Patients with missing POD 30 assessments (main endpoint) will be assigned the last value available after POD1 (if any assessment is available). A modified intention to treat population (mITT) will consider all randomised patients with Hb assessments available at POD 30 irrespective of whether they have adhered to the study protocol procedures.

The per-protocol (PP) population will consist of patients in the mITT populations who have received treatment according to the study protocol and for whom an 80% adherence to oral iron is reported and with no relevant protocol deviation that may affect main efficacy assessments (i.e. transfusion).

Although the main efficacy analysis will be performed on the PP population, the other two populations will be used for a sensitivity analysis for the main endpoint.

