One of the main limitations of the study is the lack of blinding. Masking of the different administration schedules would need a double dummy strategy which would modify the pragmatic approach of the study. Additionally, the manufacturing of placebo and the masking procedures are a hurdle for an investigator-initiated study, needing the logistic and economic support, in most cases, of the marketing authorisation holder, a situation which is not desirable for an independent trial. On the other hand, the main endpoint is based on an analytical parameter and thus it is less prone to be affected by observation bias.

In addition, while we consider that studying the QoL is a relevant endpoint, we foresee that changes in QoL will be difficult to interpret due to the health condition of patients before surgery.

In a previous observational study [14], we observed that patients treated with postoperative IVI, increased Hb levels in about 2 points at POD 30. Despite these increases, a considerable number of patients do not reach normal levels. Thus, we expect changes of this magnitude and expect them to be larger with the single dose of ferric carboxymaltose than with the fractionated doses regimen with iron sucrose. We also hypothesise that patients with lower Hb levels will benefit more from the single-dose regimen.

The study is being performed in only one centre and, in most cases, the principal investigator, an anaesthetist, is responsible for the inclusion, randomisation and treatment of the patient, ensuring uniformity of procedures. Additionally, adapted risk monitoring has been implemented to ensure that the protocol is performed according to GCP criteria and to ensure the quality of data.

The results of this study will confirm whether the single dose of 1000 mg of ferric carboxymaltose should be preferred ahead of the fractionated doses and in which type of patients this regimen should preferably be used.

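### The ITT sensitivity analysis carries an early postoperative Hb forward to POD 30, which weakens the only planned check on bias from missing POD 30 values

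*Protocol article*

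**What the plan says.** Under Populations of analysis, the protocol article defines the ITT set as "all randomised patients with at least one Hb measurement after POD 1" and adds: "Patients with missing POD 30 assessments (main endpoint) will be assigned the last value available after POD1 (if any assessment is available". The mITT set is limited to randomised patients who have a POD 30 Hb, and the per-protocol set is drawn from mITT. The main efficacy analysis uses the per-protocol set. ITT and mITT serve as sensitivity analyses of the main endpoint.

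Study procedures plans an Hb at the POD 30 visit. For other times it says that "Any additional blood tests assessing Hb levels and iron metabolism performed from patient diagnosis to end of trial" are kept, with the list "i.e. at diagnosis, immediately before surgery and on POD 4 or hospital discharge) will be recorded". POD 4 or discharge is the only point named there between POD 1 and POD 30. The Discussion puts discharge at 3 to 4 days for patients without surgical complications. It also reports that patients given postoperative intravenous iron in an earlier observational study "increased Hb levels in about 2 points at POD 30", and expects changes of that size here.

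**The concern.** Carrying the last value forward assumes that Hb stays flat from that test to POD 30. The plan expects the opposite. For most patients the carried value would come from about POD 4, some 26 days before the endpoint (30 − 4). It would stand in for a result expected to be about 2 g/dL above POD 1.

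The carried value also leaves out the period in which the arms are meant to separate. The Discussion attributes the weakness of the fractionated regimen to patients who go home before completing their dose and then depend on poorly absorbed oral iron.

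Set membership is a second weakness. A randomised patient with no Hb after POD 1 is left out, so the set is not all randomised patients and depends on something that happens after randomisation.

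What is at stake is the robustness check. Missing POD 30 values need not be random: Study procedures says that patients whose iron is stopped for intensive care admission or grade 4 complications are followed to POD 30 only where possible, and the trial is open label. Per-protocol and mITT both require a POD 30 Hb, so only ITT can show whether losing such patients matters.

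**Working it through.** **Inputs from the protocol article.** Sample size section: target difference 0.75 g/dL, SD 1.3, two-sided alpha 5%, power 80%, and a size given as "a total of 48 evaluable patients per group are to be included". Discussion: mean rise of about 2 g/dL by POD 30.

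**Assumptions, because the article gives no figure.**
- Share of patients missing POD 30 Hb: d = 10% in both arms, or 5% versus 15%.
- Mean change from POD 1 in the carried value: e = 0 to 1 g/dL, the same in both arms.
- Arm means at POD 30: 2.375 and 1.625 g/dL (average 2, difference 0.75).
- Carried values have the same SD of 1.3, and missingness is unrelated to outcome.
- ITT size: 48 per arm if imputed patients count towards the 48, or about 53 per arm if 48 have a POD 30 Hb and 10% are missing (48 / 0.9 = 53.3).
- Unadjusted comparison, normal approximation.

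**Step 1. Reproduce the plan's figure.** n = 2 × 1.3² × (1.960 + 0.842)² / 0.75² = 47.2, so 48 per group; the t-based calculation gives 48.1. With 48 per group, SE = 1.3 × √(2/48) = 0.265 and power = Φ(0.75/0.265 − 1.96) = 0.807. The planned size is right and this point does not change it.

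**Step 2. Effect of carry-forward in one arm.** With POD 30 mean μ:
- mean = (1 − d)μ + d·e
- variance = 1.3² + d(1 − d)(μ − e)²

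**Step 3. True effect 0.75, 10% missing in both arms.** The difference is 0.9 × 0.75 = 0.675 g/dL for any e common to both arms.
- e = 0: variances are 1.69 + 0.09 × 2.375² = 2.198 and 1.69 + 0.09 × 1.625² = 1.928. With 48 per arm, SE = √(4.125/48) = 0.293 and power = Φ(0.675/0.293 − 1.96) = 0.63. With 53 per arm, power is 0.68.
- e = 1: variances are 1.69 + 0.09 × 1.375² = 1.860 and 1.69 + 0.09 × 0.625² = 1.725. Power is 0.70 with 48 per arm and 0.74 with 53.

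**Step 4. No true effect, both arms rise 2 g/dL, 5% versus 15% missing.**
- e = 0: means are 0.95 × 2 = 1.90 and 0.85 × 2 = 1.70, a false difference of 0.20 g/dL. Variances are 1.69 + 0.0475 × 4 = 1.880 and 1.69 + 0.1275 × 4 = 2.200. Two-sided type I error is 0.105 with 48 per arm and 0.111 with 53.
- e = 1: means are 1.95 and 1.85, a false difference of 0.10 g/dL. Type I error is about 0.07 with either size.

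**Step 5. Direction.** With equal missingness and no true effect, the difference is 0 and type I error stays at 5%. With a true effect of 0.75 and e = 0, 10% missing on carboxymaltose and 20% on sucrose gives 0.9 × 2.375 − 0.8 × 1.625 = 0.84 g/dL. The reverse gives 0.8 × 2.375 − 0.9 × 1.625 = 0.44 g/dL. The bias can go either way.

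**The case against.** The strongest reply is that this is not the main analysis. That stands. Every per-protocol and mITT patient has a POD 30 Hb, so no carried value enters either set. A reader might infer from the power and type I error figures that the trial's primary result loses power or has an inflated error rate. The article does not support that: those figures belong to one of two sensitivity analyses.

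A second reply is that comparing ITT with mITT already shows how much the rule matters, because the two sets differ only by the carried-forward patients. That is true as far as it goes. It shows how sensitive the result is to carry-forward, but not what a plausible value for the missing patients would do. Agreement would reassure little and disagreement would be hard to interpret.

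Third, the magnitudes rest on assumptions. This also stands. The article gives no missing-data rate, and nothing beyond the open-label design and conditional follow-up after severe complications points to unequal loss. A higher early Hb, a smaller gap in missingness or a later carried value reduces the bias. The calculation is unadjusted, whereas the plan is ANCOVA. With equal missingness the rule only pulls a true effect towards no difference, which is conservative for a superiority claim.

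Two further inferences are tempting and should not be drawn. One is that clinicians choose who gets an interim test: the schedule figure is not shown and may plan that test for everyone, in which case few patients would drop out of ITT. The other is that the carried value predates any action of iron. No POD 4 change is given. The Background does describe a retrospective study followed only to discharge with no significant Hb rise, but attributes this to small size and possibly insufficient doses.

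**Conclusion.** The concern holds for the ITT sensitivity analysis only. Carry-forward is a poor rule for an outcome the plan itself expects to rise by about 2 g/dL, when the value carried is usually from POD 4 or discharge. It matters because no other planned set retains randomised patients without a POD 30 Hb.

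The actual size cannot be known from the article. Under the stated assumptions, 10% missing in both arms costs 0.075 g/dL of the 0.75 target. ITT power is then about 0.63 to 0.74, against 0.81 for 48 complete patients per arm. A 5% versus 15% imbalance with no true effect produces 0.10 to 0.20 g/dL (13% to 27% of the target) and a type I error of about 7 to 11%. The bias does not depend on the early change being exactly zero, only on its being clearly below the POD 30 change.

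Severity is moderate: worth correcting before analysis, but not a threat to the main analysis as the plan defines it.

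**What to change.** Define ITT as all randomised patients, including those with no Hb after POD 1. Replace carry-forward with multiple imputation of POD 30 Hb from POD 1 Hb, arm and any recorded in-hospital Hb, followed by the planned ANCOVA with standard multiple-imputation standard errors. A mixed model for the repeated Hb values is an acceptable alternative. Because both methods assume that missingness is explained by the observed data, add one simple delta-adjusted analysis that shifts the imputed values by arm. Keep mITT as already planned.

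The cost is a revised paragraph and a little more programming. No new data are needed, since the article already provides for recording interim Hb tests. It describes the trial as ongoing with 75 patients randomised, so on that status the change could be specified before analysis.

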## Discussion

We have designed a randomised controlled study to compare two IVI regimens to treat CRC postoperative anaemia in terms of change in Hb levels from POD 1 to POD 30. Other variables, such as percentage of patients presenting with normal Hb levels at POD 30, changes in iron metabolism parameters, safety of both IVI regimens and complications and QoL, have been considered.

According to our procedures, patients with preoperative anaemia follow an optimisation treatment with the aim of reaching adequate levels before surgery and thus minimising postoperative anaemia and the need for transfusions. In addition, in our hospital, all patients receive 200 mg of iron sucrose right after surgery to account for surgical blood loses. There are no clear recommendations on the use and efficacy of postoperative iron treatment, especially in patients who have already received IVI before surgery. In these cases, the risk of iron overload has not been demonstrated. However, there are a large number of patients who arrive at the postoperative period with Hb levels lower than desired [16, 17]. This may lead to complications, a longer hospital stay and eventually to a slower recovery.

Currently, CRC patients without surgical complications are discharged after 3–4 days. This implies that, for some patients, the treatment with fractionated IVI cannot be completed to the calculated doses and thus they are prescribed oral iron after discharge. However, the absorption of oral iron in this context is known to be minimal [1, 8–10, 12] and, together with the low compliance expected due to mild but unpleasant side effects, patients end up receiving doses lower than required. To overcome these problems, a single dose of 1000 mg is an option for patients with lower Hb levels. However, the high cost of this formulation from a commercially available brand results in an underuse of this regimen in this setting as evidenced in a previous study [14]. Thus, it is of importance to assess whether, in patients with Hb levels < 11 g/dL, treatment with single doses of IVI may lead to larger increases in Hb levels and if this benefit depends on POD 1 Hb levels or other characteristics of patients, in order to make evidence-based decisions.

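### The main efficacy analysis of a pragmatic superiority trial is per-protocol, with membership set by oral-iron adherence (mainly an iron sucrose matter) and transfusion, both of them also secondary endpoints

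*Protocol article*

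**What the plan says.** Under Populations of analysis, the Protocol article defines three efficacy sets.

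- **ITT:** randomised patients with at least one Hb value after POD 1. A missing POD 30 value is replaced by the last one available.
- **mITT:** randomised patients with a POD 30 Hb, whatever their adherence to the protocol.
- **Per-protocol (PP):** mITT patients treated according to protocol, "for whom an 80% adherence to oral iron is reported and with no relevant protocol deviation that may affect main efficacy assessments (i.e. transfusion").

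It then ranks them: "Although the main efficacy analysis will be performed on the PP population", the other two serve as sensitivity analyses for the main endpoint.

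The Background states the hypothesis that the single dose will be more effective. The Sample size section tests a difference two-sided, with no non-inferiority margin. The Discussion rejects a double dummy because it is something "which would modify the pragmatic approach of the study". Study design and interventions says that patients discharged before reaching the calculated dose go on to oral iron until POD 30. Study endpoints lists both oral-iron non-compliance and postoperative transfusions as secondary endpoints.

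**The concern.** Randomisation makes the two arms comparable at POD 1. A set selected on what patients did or needed afterwards no longer has that guarantee. Two features make this more than a formal objection here.

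First, the adherence rule can only exclude patients who were prescribed oral iron, and by the article's own account that follows mostly from an unfinished fractionated course. The Discussion explains why that regimen may fall short: oral iron is poorly absorbed and, "together with the low compliance expected due to mild but unpleasant side effects, patients end up receiving doses lower than required". Dropping non-adherent patients takes out of the comparison some of the very patients in whom the expected weakness of the iron sucrose regimen shows itself.

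Second, transfusion can follow from low Hb and itself raises Hb. Excluding on it conditions the primary endpoint on another outcome of the trial.

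At stake is the headline result. If PP and the as-randomised analyses disagree, the plan gives the main conclusion to PP, although the clinical question is which regimen to choose on POD 1.

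**Working it through.** **1. The plan's own sample size.** Inputs from the Sample size section: "the difference in change in Hb levels (primary endpoint) between the two studied regimens will be 0.75 g/dL"; "assuming a common standard deviation of 1.3"; two-sided 5%; 80% power.

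n per group = 2 × [1.3 × (1.960 + 0.842) / 0.75]² = 47.16, rounded up to 48. The stated 48 evaluable per group is reproduced. Power of the two-sample t-test at 48 per group is 79.9%.

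**2. Who meets the adherence rule.** Iron sucrose is given as 200 mg every 48 h from POD 1, and the Discussion puts uncomplicated discharge at 3–4 days. That is two doses, about 400 mg. The Ganzoni formula under Fig. 1 is weight × (target − actual Hb) × 2.4 + 500 mg above 35 kg. The article states no target Hb, so I assume 13 g/dL, with weights of 50–90 kg and Hb of 8–10.9 g/dL:

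- lowest: 50 × 2.1 × 2.4 + 500 = 752 mg
- highest: 90 × 5 × 2.4 + 500 = 1,580 mg

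All of this range exceeds 400 mg. It also exceeds 600 mg, the total if the routine 200 mg after surgery is counted. On these assumptions nearly every uncomplicated iron sucrose patient goes on to oral iron and faces the 80% rule.

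In the single-dose arm, 70 kg and Hb 10 gives 70 × 3 × 2.4 + 500 = 1,004 mg, just above 1,000 mg. The oral-iron sentence names no arm, so some single-dose patients could fall under the rule as well. Hence mainly, not only.

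**3. What selection does to the contrast.** Let a fraction f of an arm be excluded, with a mean Hb gain lower by d than that of the patients retained. The mean of the whole arm is then the retained mean minus f × d. With S for iron sucrose and F for the single dose:

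PP difference = true difference − f_S·d_S + f_F·d_F

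The first correction works against the single dose and the second in its favour. The article gives no value for any f or d.

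**4. Illustration, exclusion in the iron sucrose arm only.** Assumed: true difference 0.75, SD 1.3, 48 evaluable per arm, two-sample t-test at 5%.

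| f | d (g/dL) | PP difference (g/dL) | Power |
|---|---|---|---|
| any | 0 | 0.75 | 79.9% |
| 0.20 | 0.50 | 0.75 − 0.10 = 0.65 | 67.9% |
| 0.30 | 0.75 | 0.75 − 0.225 = 0.525 | 49.9% |
| 0.40 | 1.00 | 0.75 − 0.40 = 0.35 | 25.7% |

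**5. Same model, no true effect.** Suppose non-adherence only marks poorer recovery, and such patients are removed from the iron sucrose arm alone. For f = 20–40% and d = 0.5–1.0 the contrast is biased by 0.10 to 0.40 g/dL towards iron sucrose. In a simulation of 40,000 trials per setting with 48 per arm, the nominal 5% test rejected in 6.7% to 33.9%.

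**The case against.** **ITT and mITT are prespecified.** Any divergence will therefore be visible. This stands and limits the harm, but those analyses do not carry the main conclusion.

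**The size is speculative.** No adherence rate or Hb shortfall is documented, and d = 1.0 exceeds the whole hypothesised effect. The Discussion regards oral absorption as minimal, so missed tablets should by themselves cost little Hb. A large d would need non-adherent patients to recover worse for other reasons. This stands too: the figures are an illustration. The calculation also uses a t-test where the plan specifies ANCOVA.

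**Including transfused patients mixes the effect of transfusion into the iron comparison.** True, but the need for transfusion is part of what follows from choosing a regimen, and the supportive PP analysis can examine it.

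A reader might also infer stronger versions, which the article does not support:

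- *PP compares all single-dose patients with compliant, untransfused iron sucrose patients.* It does not. Every PP rule applies to both arms, and transfused single-dose patients are dropped too.
- *The whole failure route of the iron sucrose regimen is removed.* Only non-compliance is. Early discharge with an unfinished intravenous course is within protocol, and poor absorption affects adherent patients; both stay in PP.
- *The stopping rule excludes iron sucrose patients selectively.* The article says "Iron treatment will be discontinued in patients admitted in the intensive care unit on POD 1" for organ failure, or with grade 4 complications. Stopping under that rule is arguably treatment according to protocol, so exclusion from PP is not shown.
- *The power loss should be figured on 48 randomised per arm.* The plan says 48 evaluable, so only the calculation on that basis fits it.

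**Conclusion.** The concern holds in this form: a superiority trial about effectiveness bases its main conclusion on a set defined by post-randomisation adherence and transfusion. The first arises mainly in one arm, and both are themselves secondary endpoints. This choice is fixed in the text and the article offers no reason for it.

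The adherence rule most plausibly shifts the result against the single dose. The net direction is uncertain because transfused patients leave both arms and some single-dose patients may face the adherence rule. On the assumed inputs, an apparent difference of 0.65 to 0.35 g/dL instead of 0.75, with power of 68% to 26%, shows what is possible; it does not predict what will happen. If excluded patients gain as much Hb as those retained, the damage is confined to the loss of patients. The loss of randomised comparability does not depend on these figures.

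**What to change.** Make the primary analysis the planned ANCOVA, with POD 1 Hb as covariate, on all randomised patients in the arm to which they were assigned, regardless of oral-iron adherence, transfusion or discontinuation. Handle missing POD 30 Hb by a principled method such as multiple imputation, not by carrying forward an early postoperative value. The Discussion expects gains of about 2 points by POD 30, so an early value is a poor substitute. Keep mITT as a complete-case sensitivity analysis; it omits patients without a POD 30 value and is not the same as all randomised patients. Make PP supportive, with membership fixed before Hb results are seen by arm.

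The change needs no new assessments, and the formula still gives 48 per group with POD 30 data. The costs are a protocol amendment before database lock, in a trial already approved by the ethics committee and the medicines agency with 75 patients randomised when the article was written, and a somewhat more variable estimate that includes the Hb effect of transfusion.
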